##### Aim 1: Abstinence and Relapse

Abstinence rates at 6- and 12-months postrandomization and biochemically confirmed abstinence at 6- and 12-months postrandomization will be compared between arms using multivariable logistic regression for each outcome (6- or 12-months). Independent variables will include intervention status, strata (race and ethnicity), quitline, and covariates (as described above). We will compare time to first relapse using Cox models and Kaplan-Meier curves. The number of relapses and helping conversations will be compared between study arms using Poisson regression, with the zero-inflated Poisson or negative binomial model used if appropriate. We will carry out secondary analyses using general linear mixed models to examine change in cognitive and emotional measures of participant-reported outcomes (described above in the General Quantitative Approaches section) for participants randomized to receive Helpers Stay Quit compared to participants randomized to the usual care arm.

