## Introduction

### Background

Effective tobacco dependence treatments are more numerous and accessible than ever before [1,2]. However, tobacco use remains the leading preventable cause of premature morbidity and mortality in the United States. In addition, cessation treatments are severely underused [3-5], due to both knowledge and attitudinal barriers (eg, low awareness of and misinformation about cessation medications’ effectiveness, safety and proper use, and negative attitudes about seeking counseling or other behavioral support for quitting) [6-9]. Despite major gains in the use of smoking cessation treatment, over half of those who have recently quit will relapse within the first year. In an analysis of prospective data from a large representative sample of the general population of the United States, the risk of relapse is more than 50% [10] for abstainers with less than 12 months of abstinence. Identifying effective relapse prevention strategies will enable more individuals to maintain their abstinence beyond a year and, consequently, prevent tobacco-related morbidity and mortality.

Published research on smoking relapse prevention has limitations in methodological design and intervention approaches. Two systematic reviews of relapse prevention interventions reached differing conclusions regarding the efficacy of behavioral interventions [11,12]. Agboola et al [11] concluded minimal self-help intervention was effective. Livingstone-Banks et al [13] concluded with only “moderate certainty” that behavioral interventions were not effective, with the caveat that “further research is likely to have an important impact on our confidence,” [13] and a recommendation that future relapse prevention research examine alternative behavioral approaches [13]. A critique of extant research cited methodological weaknesses and limited conceptual approaches to treatment [13]. Different approaches to both studies of relapse prevention and to the interventions themselves are needed to advance the long-term understanding and outcomes of smoking relapse prevention. Livingstone-Banks et al recommended randomization of smokers who were already abstinent (“abstainers”) as the strongest design for relapse prevention studies [13]. The protocol for a pragmatic randomized control trial (pRCT) we present here addresses both methodological and treatment approach limitations of extant research.

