### Research Objectives

This study is designed to assess the effect of Helpers Stay Quit training on the proportion and duration of participants maintaining abstinence or relapsing over time and on participants’ personal network structure and interactions related to smoking and smoking cessation. Primary and secondary research questions are as described in study-specific aims (Textbox 1).

Textbox 1.The Helpers Stay Quit study-specific aims.Aim 1: Using a 2-group, pragmatic randomized, controlled trial (pRCT; N=940) in which abstinent smokers (2-6 weeks abstinent) are randomized to the Helpers Stay Quit intervention or quitline follow-up usual care, to evaluate the effectiveness of Helpers Stay Quit on:Smoking status (30-day and 7-day point prevalence abstinence) at 6- and 12-month intervals (primary outcome).The number, timing, and duration of participants’ lapses and relapses to smoking (secondary outcome).Rates of participants’ self-reported delivery of helping conversations to other tobacco users (secondary outcome).Aim 2: embed a mixed methods social network study into the pRCT to examine the Helpers Stay Quit effects on:Composition and structure of participants’ personal networks.Characteristics of participants’ personal networks over the course of the study (eg, proportion of smokers in personal network).Spread of smoking cessation-related information, assistance, and behaviors from participants to others in their personal networks.Recipients of helping conversations report about smoking-related interactions and information exchange with participants and associated cessation-related behavior change.Aim 3: using personal network metrics derived from the personal network study (eg, size, composition, and structure), conduct mediational analyses of personal network effects on the primary and secondary study outcomes in Aim 1.

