Participants completing every protocol activity and qualifying for every incentive could receive a total of US $419. A breakdown of the study protocol items and their compensation rates is as follows: baseline (US $20), social network assessment 1 (US $25), training (US $40), incentive for completing training within two weeks (US $10), 3-month survey (US $20), 6-month survey (US $20), 9-month survey (US $20), 12-month survey (US $20), bonus for completing all 4 surveys (US $5), social network assessment 2 (US $25), qualitative personal network interview (US $30), weekly text survey (24 total; US $4 each), biweekly text survey (12 total; US $4 each), 6-month follow-up specimen completion incentive (US $15), 12-month follow-up specimen completion incentive (US $15), and maximum completion bonus for completing all study activities (US $10).

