#### Relapse Status (Primary Outcome) and Helping Conversations (Secondary Outcome)

Smoking or other tobacco use, electronic nicotine delivery device use, use of cessation aids, and helping conversations are assessed by online surveys at baseline, 3, 6, and 12 months, and by weekly text message surveys for months 1‐6, then biweekly text surveys for months 7‐12. Relapse is defined as (1) any smoking on 7 consecutive days or (2) smoking at least once each week over 2 consecutive weeks. Multiple relapses are defined as relapsing, reporting being quit (7-day point prevalence), and then subsequently reporting smoking again. Offers of helping conversations are assessed by baseline survey and weekly text message surveys (months 1‐6), then biweekly text surveys (months 7‐12). A 5-point Likert scale queries confidence in helping conversations, for example, talking to others about quitting smoking. Content of typical helping conversation (eg, setting quit date, quit plan, cessation medication, quitline referrals, and avoiding relapse) is queried via a yes or no checklist at baseline, 3, 6, 9, and 12 months (Table 1).

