### Sample Size, Power Estimates, and Analysis

#### Power and Sample Size for Pragmatic Randomized Controlled Trial (pRCT)

A sample size of 940 participants would yield 80% power to detect a difference in smoking cessation rates between arms of 10%, assuming a conservative control arm rate of 0.25 [65], 30% dropout, and a noncontinuity corrected *χ*^2^ test. This difference is smaller than that found in the preceding pilot feasibility study (difference=46%); this effect size was chosen as a clinically significant difference with public health implications and is feasible, given the pilot results. This sample size also yields 90% power to detect standardized effect sizes for continuous secondary outcomes of Cohen *d*=0.26, a small-to-medium effect size, and considered to be a good estimate for a minimum important difference for patient-reported outcomes.

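### The named models for relapse counts guard only against over-dispersion, although the counts may instead be under-dispersed if repeat relapse is uncommon

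*Protocol article*

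**What the plan says.** In the article's Analytic Plan, under Aim 1: Abstinence and Relapse, relapse counts and helping-conversation counts are compared between arms "using Poisson regression, with the zero-inflated Poisson or negative binomial model used if appropriate". Textbox 1 (Research Objectives) lists the number, timing and duration of participants' "lapses and relapses to smoking (secondary outcome").

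The outcome section sets the first event: "Relapse is defined as (1) any smoking on 7 consecutive days or (2) smoking at least once each week over 2 consecutive weeks". It then provides for repeats: "Multiple relapses are defined as relapsing, reporting being quit (7-day point prevalence), and then subsequently reporting smoking again". Under Ethical Considerations, the payment schedule lists the reporting occasions: "weekly text survey (24 total; US $4 each") and "biweekly text survey (12 total; US $4 each"), 36 in all.

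On how common relapse is, the Background states that "the risk of relapse is more than 50% [10] for abstainers with less than 12 months of abstinence". The power section works "assuming a conservative control arm rate of 0.25". No section gives an expected mean, variance or repeat rate for the relapse count, or a power figure for comparing it.

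**The concern.** A Poisson model sets the variance equal to the mean. Zero-inflated Poisson and negative binomial relax this in one direction only, towards more variance.

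A relapse count that starts from abstinence need not go that way. A participant who relapses and never reports being quit again stays at 1. If many relapse and few do so twice, the count is close to a yes/no variable, whose variance is below its mean. Model-based Poisson standard errors are then too large, the test is conservative, and the named fallbacks cannot correct it. At stake are the confidence interval and P value for a listed secondary outcome, and in that case some of the power to see a real reduction in relapses.

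**Working it through.** **Inputs from the article.** Control abstinence 0.25, difference 10 points, 80% power, 30% dropout, uncorrected chi-square test, N=940. Relapse within a year is above 50%. In the pilot, 86% were abstinent over 6 months.

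**Assumptions.** Two-sided 5% level (not stated in the power text). A proportion p ever relapses, and each relapse is followed by another with probability r (a geometric count). The document does not give r, so a range is shown. p=0.55 stands for more than half, and 55% versus 45% applies the planned 10-point difference to it.

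**The plan's own figure.** For 0.25 versus 0.35, n = [1.96√(2×0.30×0.70) + 0.8416√(0.25×0.75 + 0.35×0.65)]² / 0.10² = 328.5, so 329 per arm. 329/0.7 = 470 per arm, or 940 in total. The figure reproduces, and 329 per arm is used below.

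**Dispersion.** The mean is p/(1−r) and D = variance/mean = (1+r−p)/(1−r). D equals 1 at r = p/2, which is 0.275 for p=0.55.

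**Test size.** With D the same in both arms, a nominal 5% Poisson test has true size 2[1−Φ(1.96/√D)], and its standard error is 1/√D times the correct one.

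**Power, worked at r=0.** The log rate ratio is ln(0.55/0.45) = 0.2007.
- Poisson SE = √[1/(329×0.55) + 1/(329×0.45)] = 0.1108.
- Correct SE = √[0.45/(329×0.55) + 0.55/(329×0.45)] = 0.0788.
- Robust power = Φ(0.2007/0.0788 − 1.96) = 72%.
- Poisson power = Φ((0.2007 − 1.96×0.1108)/0.0788) = 42%.

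| r | D at p=0.55 | With 2 or more relapses (p×r) | Poisson SE / correct SE | True size | Power, Poisson vs robust (55% vs 45%) |
|---|---|---|---|---|---|
| 0 | 0.45 | 0% | 1.49 | 0.4% | 42% vs 72% |
| 0.1 | 0.61 | 5.5% | 1.28 | 1.2% | 47% vs 65% |
| 0.2 | 0.81 | 11% | 1.11 | 3.0% | 53% vs 58% |
| 0.275 | 1.00 | 15% | 1.00 | 5.0% | no loss |
| 0.4 | 1.42 | 22% | 0.84 | 10% | over-dispersed |

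The 47% vs 65% at r=0.1 is from 10,000 simulated trials; the formula gives 48% vs 64%. Simulated sizes agree with the table within about 0.2 points.

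**Other values of p.**
- 75% versus 65% ever relapsing, taking 0.25 abstinence as a proxy for never relapsing (an assumption): 22% vs 79% at r=0, 38% vs 58% at r=0.2, with D=1 at r=0.375.
- 24% versus 14%, close to the pilot: 85% vs 89% even at r=0, a loss of about 4 points.

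**Does the fallback help?** A negative binomial was fitted to 100 simulated trials (55% vs 45%, r=0.1). Its dispersion parameter went to zero and its median SE was 0.106, the same as Poisson, against 0.087 with robust errors.

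**The case against.** The strongest reply is that under-dispersion is a supposition. The article expressly defines multiple relapses. As worded, a repeat needs only a 7-day quit report followed by smoking, a looser test than for a first relapse, and 36 text surveys can record it. Usual care tries to re-engage relapsed clients, and participants may keep using cessation aids. All this makes repeat cycles possible. It stands as a reason not to assume r is near zero, but allowing repeats does not make them frequent.

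A reader might infer that counts will be mostly 0 or 1, and that the test must therefore be conservative and lose much of its power. The document supports neither step. It gives no distribution for the count, and mostly 0 or 1 does not imply under-dispersion: at r=0.275 with p=0.55, 85% of counts are 0 or 1 and D is exactly 1. Large losses need r close to zero together with common relapse.

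The stakes are also limited. Time to first relapse is compared by Cox models and Kaplan-Meier curves. At r=0 the count only records whether a first relapse occurred, which that analysis already covers.

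Finally, the choice of variance estimator is often left to an analysis plan, which is not shown, and the article does not exclude robust errors. That is fair, and if such a plan names them the point is closed. But the article does name a base model and its alternatives, and as named they cover one direction only.

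**Conclusion.** The point holds conditionally. The stated options handle extra variation only, while the article's own relapse figures make too little variation a real possibility. The cost depends on r, which the document does not give. At 55% versus 45% ever relapsing it runs from about 30 points of power at r=0, through 18 at r=0.1 and 5 at r=0.2, to none near r=0.275. Above that the error reverses, and the negative binomial is the intended remedy.

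It would go too far to say that the interval and P value will be wrong, or that they will be too wide, because the direction cannot be known in advance. All figures rest on the geometric repeat model, 329 per arm and a two-sided 5% level. Only the relapse-count comparison is affected: the primary logistic analyses and N=940 are untouched, and the argument does not extend to helping-conversation counts.

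**What to change.** State that relapse counts are compared between arms by log-linear (Poisson-mean) regression with robust sandwich standard errors, or with quasi-Poisson standard errors, in place of choosing among Poisson, zero-inflated Poisson and negative binomial. The rate ratio keeps the same meaning, and the errors are valid for both under- and over-dispersion. In simulation at 329 per arm, robust errors kept the test size at 4.8% to 5.2% in all ten null scenarios examined.

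The cost is one line of analysis wording and one software option, with no new data. The article describes the trial as ongoing, with 12-month follow-up incomplete at submission, so the change can still be written down before the outcome is analysed.

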#### Cognitive or Emotional Measures

A dynamic model of smoking relapse is the organizing framework guiding the overall intervention and evaluation approach [14]. Selected measures evaluate possible factors in “cessation fatigue,” a latent construct proposed to contribute to “relapse proneness” and operationalized by declines in motivation, expectancy for success, coping attempts, self-efficacy, and self-control resources [14]. To explore the concept of “cessation fatigue” [16], the following patient-reported outcome measures are collected at baseline, 3, 6, 9, and 12 months post study enrollment: cessation fatigue [17], Abstinence Related Motivational Engagement – Short Form [40], smoker versus quitter identity [41], smoker group identity [41], residual attraction and vulnerability to smoking [42], situational smoking abstinence self-efficacy [43], Proactive Coping Inventory [44,45]; and Patient Health Questionnaire-4 for anxiety and depression [46-48] (see Table 1).

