#### Personal Network Study Sample Size

To measure change in personal networks at two times, 940 participants (470 in each arm) will be sufficient. Although there are few longitudinal personal network studies among those with substance use disorders or those who have recently quit using as models [55], studies using dynamic network analyses to estimate the impact of life events on an individual’s social context typically include between 33‐250 participants [66-72]. Informed by the previous feasibility study, the present personal network study features an increased sample size, a lengthened interval between the first and second personal network assessment to 1 year, and broadened the personal network name generator question to capture both strong ties and weak ties. The qualitative sample (n=60) is theory-driven; sufficient for coverage of basic consensus and range of variability of critical themes [73].

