#### Analytic Plan

##### General Quantitative Approaches

For this pRCT, descriptive statistics (mean, SD, and frequencies) will be computed for baseline participant characteristics. Participant-level covariates will be screened in bivariate analyses and included in multivariate analysis if they are related to the outcome at *P*<.2, are associated with dropout, or used in the randomization procedure. Before beginning the analyses described below to address study hypotheses, we will compare baseline characteristics of participants who drop out to participants with complete data to assess the missingness mechanism (missing completely at random [MCAR], missing at random [MAR], and missing not at random [MNAR]) and generalizability of our results [74-76]. If missingness is ignorable (MCAR and MAR), we will use likelihood-based methods that use all available data, adjusting for covariates that are associated with dropout. If missingness is nonignorable, we will use pattern mixture models. Sensitivity analyses with multiple imputation will be undertaken if missing data rates for the primary outcome are greater than 10% at any follow-up time used in the analysis.

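### The mixed models of change in the patient-reported scales do not name each scale's own baseline score as a covariate; naming it is a free gain in precision for secondary analyses

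*Protocol article*

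**What the plan says.** All places are in the protocol article.

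- **Cognitive or Emotional Measures** lists eight scales and says that "the following patient-reported outcome measures are collected at baseline, 3, 6, 9, and 12 months post study enrollment". Under **Prerandomization Run-in/Baseline Measures**, anyone who does not complete the baseline procedures is not randomised. Every randomised participant should therefore have a baseline score.
- **Aim 1: Abstinence and Relapse** plans "general linear mixed models to examine change in cognitive and emotional measures of participant-reported outcomes" for the intervention arm against usual care, as secondary analyses. For the abstinence models the same section lists the independent variables: arm, race and ethnicity, quitline and covariates. For the scales it lists none and does not mention the baseline score.
- **General Quantitative Approaches** gives the covariate rule: "Participant-level covariates will be screened in bivariate analyses and included in multivariate analysis if they are related to the outcome at" P<.2, or if they are associated with dropout or were used in the randomisation. A scale's own baseline score is neither named nor excluded.
- **Power and Sample Size for Pragmatic Randomized Controlled Trial (pRCT)** states: "This sample size also yields 90% power to detect standardized effect sizes for continuous secondary outcomes of Cohen" *d*=0.26. It does not say which SD standardises d, what correlation with baseline is assumed, or which analysis the figure belongs to.

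**The concern.** When a mixed model is said to examine change and baseline is one of the repeated responses, the ordinary arm-by-time contrast at a visit is the difference between arms in mean change from baseline. With randomised arms that contrast is unbiased, but it carries the full noise of the baseline score. Adjusting the follow-up scores for baseline, or constraining the two arms to a common baseline mean, estimates the same effect with smaller variance.

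The baseline scores are already collected, so precision would be given up for nothing. Two things are at stake, both secondary: the width of the intervals for eight scales, and the link between the analysis and the 90% power statement. There may also be a knock-on effect. The Aim 3 mediation analysis screens changes in these scales for association with arm at P=.1, and a noisier contrast makes it easier to miss a true mediator.

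**Working it through.** **Inputs from the protocol article.** The total is "940 participants (470 in each arm) will be sufficient" (Personal Network Study Sample Size). The primary power calculation works "assuming a conservative control arm rate of 0.25 [65], 30% dropout, and a noncontinuity corrected" χ² test. With 30% dropout, 470 × 0.70 = 329 per arm. The target is d=0.26 at 90% power.

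**Assumptions, not in the document.** Two-sided alpha of 0.05; equal SD at baseline and follow-up; baseline-to-follow-up correlation r between 0.3 and 0.7.

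**Step 1: reproduce the plan's figures.** Power = Φ(d/s × √(n/2) − 1.96), where s is the SD of the analysed quantity in raw-score SD units.

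- Plain comparison, s=1: 0.26 × √(329/2) = 0.26 × 12.83 = 3.33; 3.33 − 1.96 = 1.37; power 91.5%. The difference detectable with 90% power is 3.24/12.83 = 0.253. The stated 90% at d=0.26 is reproduced.
- The same alpha and 329 per arm give 80.1% for 25% against 35% abstinence, matching the primary calculation. This supports the alpha assumption.

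**Step 2: variances at one visit.**

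- Change from baseline: s² = 2(1−r).
- Baseline-adjusted: s² = 1−r².
- Difference: 2(1−r) − (1−r²) = (1−r)², never negative.
- Ratio, change to adjusted: 2(1−r)/[(1−r)(1+r)] = 2/(1+r).

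**Step 3: numbers, 329 per arm, d=0.26 in raw-score SD units, single visit.** The last two columns give the total N for 90% power, including 30% dropout.

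| r (assumed) | 2/(1+r) | Power, change | Power, adjusted | N, change | N, adjusted |
|---|---|---|---|---|---|
| 0.3 | 1.54 | 80.5% | 93.8% | 1246 | 809 |
| 0.4 | 1.43 | 86.1% | 95.3% | 1069 | 749 |
| 0.5 | 1.33 | 91.5% | 97.1% | 889 | 669 |
| 0.7 | 1.18 | 99.0% | 99.7% | 535 | 455 |

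**Step 4: where change drops below 90%.** This needs s² above (0.26 × 12.83/3.24)² = 1.058. Setting 2(1−r) = 1.058 gives r = 0.47. The adjusted s² is never above 1, so adjusted power is never below the 91.5% of Step 1.

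**Step 5: other readings of the plan.**

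- If d is in SD units of the change itself, power for the change analysis is 91.5% whatever r is.
- If the contrast averages the four follow-ups under compound symmetry, s² for change is (1+3r)/4 + 1 − 2r. At r=0.3 this is 0.475 + 1 − 0.6 = 0.875, and power is 94.6%. The adjusted s² is (1+3r)/4 − r² = 0.475 − 0.09 = 0.385. The 90% is met either way, but the ratio is 0.875/0.385 = 2.27, so the efficiency gap is wider than at a single visit.
- If the baseline score is a candidate in the P<.2 screen, it passes with probability essentially 1 at r=0.3 with 658 participants (about 90% at r=0.1).

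**The case against.** The strongest reply is that the plan does not say the baseline score is left out. Examining change is compatible with an arm-by-time model with free baseline means, with a common baseline mean, or with follow-up scores adjusted for baseline. The last two are already efficient. The exact form of the model is something a condensed article may leave to an analysis plan that is not shown. This stands: a reader might infer that the scales will be analysed without baseline adjustment, but that inference rests on silence.

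The P<.2 rule is a second reply, and it partly stands. If the baseline score counts as a candidate it will almost surely enter. If baseline is one of the responses, it is not a candidate covariate at all, and the rule does nothing.

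Third, a reader might infer that the 90% power claim is wrong. The documents do not support that. The figure reproduces, and a shortfall needs all of the following together: no adjustment or constraint, a single-visit contrast, d on the raw-score SD, and r below about 0.47. Nor can the completion figure in the Results section (337 participants, 65%) be used to lower the analysed number to 65% of each arm. It is an interim count with no stated denominator, and 337/940 is 36%.

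Finally, chance baseline imbalance costs precision in a change contrast but does not bias it over randomisations, and these are secondary analyses on which no abstinence conclusion depends.

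After all this, one thing remains: the article names change as the target and does not name the one covariate that would make the comparison efficient.

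**Conclusion.** The point holds as a minor one about secondary analyses. The plan does not state adjustment for each scale's own baseline score, and the covariate screen does not guarantee it. On the ordinary reading, with baseline as a free response, a single-visit contrast needs 2/(1+r) times the information of the adjusted one: 1.18 at r=0.7 and 1.54 at r=0.3. The direction holds for every r below 1. The size rests on an assumed r and on equal SDs at the two times.

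The stated power stands. Under the single-visit, raw-SD reading, unadjusted change gives 80.5% to 99.0% over the assumed range of r, and adjustment gives 93.8% to 99.7%. What the power statement lacks is a declared SD unit and a link to the planned model.

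**What to change.** In Aim 1: Abstinence and Relapse, state that for each scale the mixed model is fitted to the 3-, 6-, 9- and 12-month scores with the scale's own baseline score, quitline and race/ethnicity as covariates, or that baseline is kept as a response with means constrained equal across arms. Report the adjusted arm difference at each visit. In the power section, say that d=0.26 is in raw-score SD units under that model.

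The cost is a sentence in one section and a clause in another. No new data are needed and there is no material downside. Enrolment is complete but the trial is described as ongoing, so the wording can still be fixed before the analysis.
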